### Infant Breast-Feeding Assessment Tool (IBFAT)

Various tools or tests to assess lactancy have been developed. The IBFAT tool was developed and published by Matthews et al. in 1993 to evaluate the behavior of the baby during sucking and swallowing, with a reliability of 91 % [17]. Using six items, the behavior of the baby was quantified and evaluated during lactancy in the first week of life and the focus was concentrated on both the baby and the mother.

Schlomer et al. [18] evaluated two scores as tools to assess lactancy, to correlate problems during lactancy and the degree of maternal satisfaction. The LATCH tool, which is a system for the documentation of lactation, identifies areas where intervention is required to support lactancy and focuses on the role of the mother in the process of breastfeeding whereas the IBFAT scale focuses on the baby during feeding. They found that as the scores of both instruments increased there was a tendency to an increase in maternal satisfaction with a decrease in breastfeeding problems, but this was not statistically significant (LATCH *r* = 0.5, *p* = 0.06 and IBFAT *r* = 0.49, *p* = 0.06).

Riordan et al. [19] initially included the IBFAT, MBA (Mother-Baby ASSESS tool) and LATCH tools to assess the reliability and validity of three clinical assessment instruments for lactancy evaluation. They found that the coefficient reliability was not acceptable for clinical decision-making. Subsequently, Altuntas et al. [20] in 2104, again assessed the validity and reliability of these three scales, finding a positive and significant correlation; the MBA tool had a correlation ranging from 0.81 to 0.88, the IBFAT from 0.9 to 0.95, and the LATCH tool between 0.85 and 0.91. They concluded that the three scales or tools are compatible, reliable, and appropriate to evaluate the efficiency of lactancy.

### Objectives

To determine the effect of immediate versus early SSC birth on the duration of exclusive human lactancy in healthy, full-term newborns in the Universidad de La Sabana Clinic.

### Specific objectives

To evaluate the competence of the newborn human lactancy in the first 24 h of life by using the IBFAT instrument among newborns in immediate SSC compared with early SSCTo determine the prevalence for hospitalization and admission to the neonatal intensive care unit (NICU) in the first week of life between the two SSC groups (immediate versus early)

### Hypothesis

○ Null hypothesis: there is no difference in the percentage of healthy, full-term newborns receiving exclusive human breastfeeding for three or more months between the immediate versus early birth SCC groups: relative risk (*RR*) = 1○ Alternative hypothesis: there is a difference in the percentage of healthy, full-term newborns receiving exclusive human breastfeeding for three or more months between the immediate versus early birth SCC groups: *RR* ≠ 1

## Methods/design

### Participants, interventions, and outcomes (see: Table 2 Schedule of enrolment, interventions, and assessments)

#### Participants

Included healthy, full-term newborns treated at the Universidad de La Sabana Clinic who meet the following criteria:○ Inclusion criteria:▪ Infants of mothers who prenatally express their desire to breastfeed their newborn baby▪ Full-term newborns who are defined, by obstetric method and confirmed by pediatric method (Ballard), as being between 37 and 42 weeks of gestation with appropriate weight for gestational age (between 10^th^ and 90^th^ percentiles for gestational age)▪ Delivered by vaginal birth▪ Do not require basic or advanced neonatal resuscitation maneuvers▪ Have healthy and stable cardiorespiratory systems at birth▪ Have been permitted to room with the mother
○ Exclusion criteria:▪ Mothers and newborns who present absolute or relative contraindications for human lactancy▪ Multiple pregnancies and births▪ Mothers with postpartum complications that limit the onset of human lactation▪ Major fetal congenital malformations that prevent human lactation

#### Interventions

According to the assigned group, early or immediate SSC will take place.

##### Early SSC group (control group)

At birth, the baby will be dried and placed on the abdomen and chest of their mother where thermoregulation maneuvers are applied once cord clamping has been completed. At this time, the baby will placed under the radiant heat lamp in order to complete all newborn adaptation interventions. Once stable, the mother and the baby will proceed with the initiation of SSC for at least 1 h or until the baby has completed the first lactation adequately; SSC will be allowed to continue if the mother expresses a desire to do so. During SSC, the mother and baby will receive monitoring by health personnel. All adaptation interventions, mediate and immediate (Table 3), in the newborn will take place under the radiant heat lamp during the first postnatal hour.

**Table 2 Tab2:**
[figure not shown]
Schedule of enrollment, interventions, and assessments

**Table 3 Tab3:** Adaptation interventions

Immediate adaptation interventions	Mediate adaptation interventions
• Cleaning of the airways • Drying and stimulating newborn thermoregulation • APGAR rating • Cord clamping • Identifying the newborn • Taking a blood sample from a segment of placental cord for blood group and congenital hypothyroidism screening	• Evaluation of sex and initial physical examination • Application of vitamin K and eye infection prophylaxis • Anthropometric measures

##### Immediate SSC (intervention group)

At birth, the baby will be dried and placed at the mother’s breast where thermoregulation maneuvers will be applied and, once cord clamping has taken place, the baby will be left in SSC with the mother where the immediate neonatal adaptation interventions will take place. Mother and baby will be left in SSC for at least 1 h or until the baby has completed its first lactation properly. Once completed, the baby will be taken to the heat lamp to perform and complete all the newborn mediate adaptation interventions. If the mother expresses the desire to continue in SSC, this will be allowed again after these interventions. During immediate SSC, mother and baby will receive continuous monitoring by the health staff.

#### Outcomes

##### Primary outcome

Exclusive human lactancy for three or more months: exclusive human lactancy is defined as the time in months with human lactation as the only food source and without having received other liquids or solid foods (except drugs and/or vitamins).

##### Secondary outcomes

Human lactation capacity in the newborn within the first 24 h of life and prior to discharge using the IBFAT scale (Table 4)Maternal satisfaction with breastfeeding in the first 24 h according to the IBFAT scale (Table 4)Evolution of birth weight in the first week of lifeThe need for hospitalization in the neonatal care unit in the first week of life

##### Instruments and times to assess the results

Newborn capacity for human lactation: the Infant Breastfeeding Assessment Tool – IBFAT (newborn human lactancy behavior) within the first 24 h of life and prior to discharge
Measurement of the change in weight from birth to the end of the first week of life: this will only be done with a previously calibrated electronic scale, which will take measurements at birth and in the first week of life. The need for admission to the NICU in the first week of life will be assessed during the first follow-up visit in the first the week of life (Additional file 1)Duration of exclusive human lactation: monthly telephone tracking of breastfeeding status will continue for 6 months or until human lactation is no longer the only food source (Additional file 2)

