### Sample size

24 % babies in Colombia, received exclusive breastfeeding up to 5 months old (9). This was the baseline risk assumed for the sample size calculation [9]. No studies were found that comparing different strategies from SSC; so that estimate the sample size, information 2014 Cochrane meta-analysis was used [3], which compares SCC (regardless of the starting time) with nonintervention. In this meta-analysis, SSC increases exclusive human lactancy in babies of 3 − 6 months of age (RR 1.97, 95 % CI 1.37 to 2.83). With the information of exclusive breastfeeding for Colombia and the effect of SCC﻿, report in the meta-analysis, was estimated ﻿a sample size of 300 newborns. This sample was calculated, two tailed, for a type I error of 5 %, a type II error of 20 %, and an estimated loss rate of 30 %. Will be included 150 newborns per study group.

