### Statistical methods

Descriptive analyses were performed using measures of central tendency (median, average), location (percentiles) and dispersion (standard deviation and ranges) for continuous variables and absolute frequencies and relative for the categories. Bivariate analysis will be performed to determine which variables (evaluation interventions and others) are associated with exclusive lactancy at 6 months. In the continuous variables, the Student’s *t* test will be used for independent samples or the Wilcoxon rank sum test when the assumptions of normality for the *t* test are not fulfilled. The assumption of normality will be evaluated with the Shapiro-Wilk and Kolmogorov-Smirnov tests. Contingency tables will be constructed in the categorical variables, assessing the independence between variables with the chi-square test, or Fisher’s exact test when the assumption of number of cases per cell in the contingency tables, multiplied by two, is not fulfilled. The relative risk (RR) will be calculated as an effects measurement with confidence intervals, adjusted measurements will be calculated using a multivariate Poisson regression model, for adjustment variables with significant results those with biological plausibility will be used in the bivariate analysis. An analysis will be carried out for a two-tailed type I error level of 5 %. The Stata 11 program will be used for the data analysis. An interim analysis will be performed upon submission of half of the expected events (106), setting the limits for early termination of the trial according to the methods proposed by Pampallona and Tsiatis 1994 [21].

The protocol study information will be revised by the Data Monitoring Committee used by the clinic and recruited for the study. This committee will assess the study’s progress, safety data, and critical efficacy endpoints. The DMC reviews unblinded information during the conduct of the study. The information will be periodically revised every 2 weeks.

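### On the natural reading, first-week weight change is analysed by a t test or a Wilcoxon test picked by two normality tests with no tie-break, so its effect measure is not fixed in advance

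*Protocol article*

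**What the plan says.** - **Outcome.** Weight evolution in the first week is listed under Secondary outcomes. Instruments and times to assess the results describes it as "Measurement of the change in weight from birth to the end of the first week of life", from electronic-scale weights taken at birth and in the first week.
- **Test.** Statistical methods, like the Abstract, sends continuous variables to Student's t test for independent samples, or to the "Wilcoxon rank sum test when the assumptions of normality for the" t test do not hold.
- **Choice of test.** "The assumption of normality will be evaluated with the Shapiro-Wilk and Kolmogorov-Smirnov tests". The text gives no level for these tests, does not say whether they are run per arm or pooled, does not say which version of Kolmogorov-Smirnov is meant, and has no rule for disagreement.
- **Adjustment.** The only adjusted model named is Poisson regression for the relative risk.
- **Level.** "An analysis will be carried out for a two-tailed type I error level of 5" per cent.

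The paragraph introduces these tests as a search for variables, the interventions among them, associated with exclusive breastfeeding at 6 months. It does not say outright that they compare weight change between arms. No other method for a continuous outcome is given.

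**The concern.** A t test and a Wilcoxon rank sum test do not report the same quantity. The first gives a mean difference in grams, which can be read clinically and pooled with other trials. The second tests a shift in ranks. If a preliminary test on the trial's own data selects between them, the effect measure is unknown until the data are in. With two preliminary tests of very different sensitivity and no tie-break, the written rule may not select either. An analysis plan that followed this text would inherit the ambiguity.

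The same sentence leaves the comparison unadjusted, although birth weight is recorded. Subtracting a baseline does not remove all dependence on it, so some precision may be lost.

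**Working it through.** **Inputs.** Two-sided 5% level (Statistical methods). "Will be included 150 newborns per study group" (Sample size), less the planned 30% loss: 150 × 0.70 = 105 per arm. Applying that loss to a first-week outcome is my assumption. The documents give no SD of weight change, no distribution and no correlation with birth weight. All three are assumed below, and the ranges are shown.

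**The plan's own figure.** None is stated for a continuous outcome. The total of 300 was set for the binary primary outcome from 24% and RR 1.97 (0.24 × 1.97 = 47.3%). The usual two-proportion formula at 80% power gives 66 per arm, 66 / 0.70 = 95 with loss, 190 in total, so 300 is not reproduced. That does not bear on this point.

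**Step 1: how often the two normality tests disagree.** Simulated percentages (3,000 samples per row at n = 105, 1,000 otherwise). KS is Kolmogorov-Smirnov with estimated mean and SD and uncorrected critical values; Lilliefors is the corrected version.

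| Assumed shape | n | Shapiro-Wilk rejects | KS rejects | Lilliefors rejects | Disagree, KS | Disagree, Lilliefors |
|---|---|---|---|---|---|---|
| Normal | 105 | 4.6 | 0 | – | 4.6 | – |
| Normal | 300 | 5.4 | 0.1 | 3.6 | 5.3 | 5.6 |
| Skewness 0.5 | 105 | 45 | 0.5 | – | 44 | – |
| Skewness 0.5 | 150 | 58.0 | 0.9 | 25.7 | 57.1 | 36.3 |
| Skewness 0.5 | 300 | 87.0 | 3.4 | 49.5 | 83.6 | 40.1 |
| t, 5 df | 300 | 93.1 | 13.8 | 65.4 | 79.3 | 28.3 |
| Skewness 1 | 150 | 99.6 | 20.9 | 81.8 | 78.7 | 17.8 |
| Skewness 1 | 300 | 100 | 68.0 | 98.7 | 32.0 | 1.3 |
| 0–12 integer score | 150, 300 | 100 | 100 | 100 | 0 | 0 |

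Over n = 105 to 300, for t tails with 5 df or skewness 0.5, disagreement is 42–84% with uncorrected KS and 27–40% with Lilliefors.

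**Step 2: what the choice of test changes.** 105 per arm, 3,000 simulated trials per cell, true difference 0 or 0.387 SD. The latter is the difference detectable with 80% power: (1.960 + 0.842) × √(2/105) = 0.387.

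| Shape | Power, t | Power, Wilcoxon | Different verdict at 0.387 SD | Different verdict under the null |
|---|---|---|---|---|
| Normal | 80.9% | 78.7% | 5.3% | 2.1% |
| t, 5 df | 79.4% | 86.3% | 9.6% | 3.1% |
| Skewness 0.5 | 80.5% | 80.5% | 5.7% | 1.8% |
| Skewness 1 | 79.6% | 85.3% | 8.9% | 3.4% |

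Type I error of the two-stage choice was 4.8–5.3% over all shapes tried, including the 0–12 score. With a simulation error of √(0.05 × 0.95 / 3000) = 0.4 percentage points, that is indistinguishable from 5%.

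**Step 3: what adjustment for birth weight adds.** With r the correlation of weight change with birth weight, the residual SD is SD × √(1 − r²), so the variance falls by r².

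| r (assumed) | Variance cut | Power, from 80% | Detectable difference, 105 per arm |
|---|---|---|---|
| 0 | 0 | 80.0% | 0.387 SD |
| 0.1 | 1% | 80.4% | 0.385 SD |
| 0.2 | 4% | 81.6% | 0.379 SD |
| 0.3 | 9% | 83.6% | 0.369 SD |
| 0.5 | 25% | 89.9% | 0.335 SD |

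A birth-weight imbalance of one standard error is √(2/105) = 0.14 SD. It moves the unadjusted difference in change by r × 0.14, that is 0.014 to 0.04 SD at r = 0.1 to 0.3.

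**The case against.** The best defence has five parts.

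- **The protocol never assigns these tests to weight change.** That is correct as to wording. But weight change is a listed outcome and no other method is offered, so the reading is natural. It remains an inference.
- **Covariate adjustment of a secondary outcome is commonly left to an analysis plan, and an unadjusted comparison of change is valid in a randomised trial.** This stands. Lack of adjustment alone would be no finding. The rule for choosing the test is different, because this document states it.
- **The analyst works with coded arms (Masking).** This limits steering towards a favoured arm. It does not settle which test is run, nor prevent both p-values being seen.
- **Birth weight makes a doubtful covariate.** Anthropometry is a mediate intervention (Table 3). In the immediate group it follows at least an hour of contact or the first feed; in the early group it falls within the first postnatal hour. This is worth clarifying, but it applies equally to the plan's change score, which subtracts the same weight.
- **Little follows from it.** This is largely right, as Steps 2 and 3 show.

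A reader might infer more than the documents support: that birth weight is ignored (it is already subtracted); that false positives are inflated (they are not); that the two normality tests will often disagree as a matter of fact (this depends on an unstated distribution and test version); or that the IBFAT comparison is also undetermined (on a coarse 0–12 score both tests reject, so the written rule leads to Wilcoxon).

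**Conclusion.** The point holds as a minor one about a stated method. The rule in Statistical methods does not determine a single analysis, and on the natural reading it leaves the effect measure for first-week weight change open until the data are seen.

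The cost is an effect measure that is not prespecified, plus a verdict that can turn on the choice of test. The 5–10% of trials at about 80% power (2–3% under the null) is a ceiling: the missing tie-break matters only when the normality tests also disagree. The precision forgone is small unless r is about 0.3 or more.

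All of these sizes rest on assumed shapes and correlations, on 5% normality tests, and mostly on 105 infants per arm. The primary outcome and the sample size are not touched.

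**What to change.** In Statistical methods:

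1. Remove the normality tests as the means of choosing an analysis.
2. For weight, prespecify one linear model of first-week weight on arm and birth weight with robust standard errors, and report the adjusted mean difference in grams with a 95% confidence interval. Using change as the response gives the same arm coefficient once birth weight is in the model.
3. Use age at weighing only in a sensitivity analysis. It is recorded after randomisation, and the documents give different windows: 3 to 10 days in the Abstract, the first week in Follow-up and in Instruments and times to assess the results. Those passages should be reconciled.
4. State when birth weight is measured in each arm, reconciling the two intervention descriptions and Table 3 with the weighing at birth.
5. For the IBFAT score, name the Wilcoxon rank sum test directly.

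The cost is a few sentences and slightly more modelling. It needs no new data and no change in sample size, and the article states that recruitment has not opened.

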**Methods/design:**

A randomized, blind clinical trial will be performed with full-term healthy newborns born at the Universidad de La Sabana Clinic. The blind trial participants will be those persons measuring the results and analyzing the data. The sample size will be calculated for a type I error of 5 %, a two-tailed type II error of 20 %, and an estimated percentage loss of 30 %; 150 infants will be included in each group. Randomization will be performed using permuted, size-6 blocks. Descriptive analysis will be conducted using central tendency and dispersion measurements. A bivariate analysis will be performed to determine which variables are associated with exclusive lactancy at 6 months. For continuous variables, Student’s *t* test will be used for independent samples, and the Wilcoxon rank sum test will be used if the assumptions of normality for the *t* tests are not fulfilled. The assumption of normality will be evaluated using the Shapiro-Wilk and Kolmogorov-Smirnov tests. Categorical variables in contingency tables will be constructed to assess the independence between variables using the chi-square test, or Fisher’s exact test when the assumption of the number of cases is not met by the values in the contingency tables multiplied by two. This will be calculated as a measurement of the effect of relative risk (RR) with confidence intervals; the adjusted measurements will be calculated using a multivariate regression Poisson model. Variables with significant results will be used in the bivariate analysis, and those with biological plausibility will be used for the adjustment. The analysis will be carried out for a two-tailed type I error level of 5 %. The Stata 11 program will be used for data analysis. An interim analysis will be performed upon the submission of half the expected events (106), setting limits for the early termination of the trial according to the method proposed by Pampallona and Tsiatis (1994). Intervention: There will be two SSC randomization groups: early versus immediate. After completing the neonatal adaptation process and based on the group assignment, the mother will be left with her newborn child in hospital accommodation. Prior to discharge, the Infant Breast-Feeding Assessment Tool (IBFAT) will be applied. Monitoring will initially be performed with a face-to-face assessment between 3 and 10 days of life, followed by monthly telephone calls for 6 months to verify lactation status.

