### Study procedures

#### Prior to birth

▪ Prior to the start of the study, health personnel (nurses, pediatricians, and obstetricians) will undergo training regarding: SSC after birth in healthy newborns, human breastfeeding concepts (technical, definition of exclusive lactancy and its effective benefits and contraindications), the institutional human lactation protocol and management of the mothers with their newborn baby▪ The mothers who meet the entry criteria will be identified in the obstetrics and gynecology outpatient department at their prenatal appointment. An obstetric history will be conducted by the physician in order to identify risk factors or conditions that may contraindicate the study. Those mothers who meet the criteria for inclusion will be interviewed in order to explain the purpose of the study, its application and other events to be expected. Should they accept the offer of participation, they will sign an informed consent (Additional file 3) and their personal data, telephone number, and email address will be collected for follow-up▪ Those pregnant women who meet the inclusion criteria and sign an informed consent will be classified randomly using opaque envelopes allocated to the intervention or control group. Each envelope will be coded and assigned a study entry number. Prior to delivery, health professionals can determine what the intervention will be and prepare all their personnel to support the mother and child

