#### Follow-up

▪ The first assessment will take place in the first week of life. The mother and the baby will be summoned to the Universidad de La Sabana Clinic and a nursing professional will perform it. This consultation aims to record the birth weight, the effectiveness of human lactation and feeding capacity and the need for hospitalization.▪ Monthly follow-up. This follow-up procedure will take place via monthly telephone calls with the mothers for 6 months, checking their adherence to human lactancy and, in the cases where breastfeeding has been suspended, inquiring about the reasons for this.

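### First-week neonatal unit admission has one named point of ascertainment, a return visit, and a rooming-in criterion settled after randomisation, so some infants may be dropped or missed because they were admitted

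*Protocol article*

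**What the plan says.** The Protocol article makes first-week hospitalisation and neonatal intensive care admission a specific objective (Specific objectives) and lists first-week neonatal unit hospitalisation under Secondary outcomes.

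**Ascertainment.** Instruments and times to assess the results states: "The need for admission to the NICU in the first week of life will be assessed during the first follow-up visit". It refers to Additional file 1, which is not shown. Follow-up describes the visit: "The mother and the baby will be summoned to the Universidad de La Sabana Clinic and a nursing professional will perform it". Its purposes are weight, "the effectiveness of human lactation and feeding capacity and the need for hospitalization". That section places it in the first week of life; the abstract gives a "face-to-face assessment between 3 and 10 days of life". The later monthly calls are described as covering breastfeeding status only.

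**Eligibility.** Among the inclusion criteria in Participants are "Have healthy and stable cardiorespiratory systems at birth" and "Have been permitted to room with the mother".

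**Randomisation.** Prior to birth states: "Those pregnant women who meet the inclusion criteria and sign an informed consent will be classified randomly using opaque envelopes". It adds: "Prior to delivery, health professionals can determine what the intervention will be".

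**Analysis set.** The Intention-to-treat analysis section keeps all study participants in their randomised group and adds best-case and worst-case estimates for those lost to follow-up.

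**The concern.** Both rules can depend on the event being counted. An infant sent to the neonatal unit soon after birth may not be allowed to room in, and so may fail an inclusion criterion because of the admission. An infant in another hospital cannot be brought to a visit at the clinic. If such infants leave the analysis or go unrecorded, the prevalence named in the objective is too low. The comparison is also at risk if contact timing changes early admissions. The Background section points to that period: it motivates the intervention partly by cardiorespiratory and thermal stability and by less hospitalisation in the first week.

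**Working it through.** The documents give no admission rate and no precision target for this outcome, so there is no stated figure to reproduce. The check is first a reading of the sequence, then an illustration.

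**1. Order of events**

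- Pregnancy: consent, then randomisation; staff can know the arm before delivery (Prior to birth).
- Birth: stability is judged and the assigned care starts.
- Control arm: all adaptation steps are done under the lamp in the first postnatal hour. Intervention arm: the mediate steps, which include the initial physical examination (Table 3), follow at least an hour of contact or the first completed feed.
- Joint accommodation follows adaptation (abstract).

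Permission to room in is therefore settled after randomisation. That it also comes after assigned contact has begun is an inference from this order; Participants gives no time for it.

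**2. Which admissions the stated rules would record**

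| Infant | Rooming-in criterion | Recorded at the visit? |
|---|---|---|
| Admitted straight from birth, never roomed in | Not met | Unclear; lost if treated as ineligible |
| Roomed in, admitted, home before the visit | Met | Yes |
| Roomed in, in the clinic's own unit at visit time | Met | Can be: already on site |
| Roomed in, hospitalised elsewhere throughout, or not brought | Met | No |
| Roomed in, seen on day 3, admitted on days 4 to 7 | Met | No |

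**3. Illustration**

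The only documented input is 150 infants per arm (Sample size). All rates are assumptions:

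- *a*: admitted straight from birth and treated as ineligible
- *b*: roomed in, admitted, and recorded at the visit
- *c*: roomed in, admitted, and not brought to the visit

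Risk in all randomised infants = *a* + *b* + *c*. Recorded risk = *b* / (1 − *a* − *c*). Take *b* = 2% and *c* = 1% in both arms, and vary *a* (immediate v early).

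| *a* | All randomised | RR | Recorded | RR |
|---|---|---|---|---|
| 2% v 2% | 5% v 5% | 1.00 | 2.06% v 2.06% | 1.00 |
| 2% v 6% | 5% v 9% | 0.56 | 2.06% v 2.15% | 0.96 |
| 6% v 2% | 9% v 5% | 1.80 | 2.15% v 2.06% | 1.04 |

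For the second row: 0.02/(1 − 0.02 − 0.01) = 2.06%; 0.02/(1 − 0.06 − 0.01) = 2.15%; ratio 0.96. The share of admissions recorded is 2/5 = 40% v 2/9 = 22%. Per 150 infants, that is 3 recorded in each arm out of 7.5 and 13.5.

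With *b* = 3% and *c* = 2%, the three relative risks are 1.00, 0.64 and 1.57 in all randomised infants, against 1.00, 0.96 and 1.04 recorded.

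**4. Precision with complete capture**

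At an assumed 6% risk (9 of 150 per arm), SE(log RR) = √[2(1/9 − 1/150)] = 0.457. The 95% limits are the estimate multiplied and divided by exp(1.96 × 0.457) = 2.45.

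**The case against.** The article says when admission is assessed. It does not say that the visit is the sole source or that clinic records are excluded, and Additional file 1 may add detail. Statistical methods also has a monitoring committee reviewing safety data every two weeks, so some reporting may run outside the visit. The visit is at the clinic where the infants are born, so one in its own unit is on site, and any infant admitted and home again before the visit is counted. Mothers receive a study number and are randomised before delivery, so they can be read as participants under the intention-to-treat section; a missed visit can be read as a loss covered by the best and worst cases. The outcome would be imprecise even with complete capture.

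Much of this stands. A reader might infer that admission is counted only in infants who roomed in and came back, and that an infant failing the rooming-in criterion is no longer a participant. No section says either.

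What remains is that no other source is named, and that the intention-to-treat section does not settle the status of a randomised infant who fails a criterion judged after birth. Best-case and worst-case estimates would also treat as missing an admission that records could show.

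**Conclusion.** The point holds as a weakness in ascertainment and an unresolved conflict between Participants, Prior to birth and Intention-to-treat analysis. As written, the plan allows infants admitted straight from birth to be dropped. It can also miss those hospitalised elsewhere, not attending, or admitted after an early visit. Prevalence would then be understated. The relative risk is at risk only if the lost admissions differ by arm; with equal early admissions it is essentially unchanged.

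A reader might go further and infer that most admissions go uncounted, or that a real effect will appear as none. The documents do not support that. The shift from 0.56 to 0.96 arises because the whole difference was placed in the group assumed to be lost, and the reversed assumption pulls 1.80 to 1.04. Neither size nor direction can be derived from the protocol. This concerns a secondary outcome, though a stated objective, and is worth correcting because correction is easy.

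**What to change.** - In Instruments and times to assess the results and in Follow-up: record neonatal unit admission from birth to day 7 for every randomised infant from the clinic's own admission records, whatever the rooming-in status or visit attendance. Keep the visit as a supplementary source.
- Add one question on first-week admissions elsewhere to the month-1 call already planned.
- In Intention-to-treat analysis: state that a randomised infant not roomed in because of admission stays in the analysis of this outcome and counts as an event, and reconcile this with Participants and Prior to birth.

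The rooming-in criterion need not be deleted. Removing it would change the target population and the primary analysis set, a debatable trade-off for one secondary outcome. Fixing the day of the visit alone would not reach infants who cannot be brought to it.

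The cost is a record look-up, one extra call question and a few admitted infants kept in the analysis of this outcome. Because Randomization has the allocation written in the medical record, the look-up should be arranged so that outcome assessors stay blind. The article reports that recruitment has not opened, so the change can be made before any data exist.
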